## Abstract

**Background:**

Subthreshold depression refers to a state of mental sub-health that has depressive symptoms but does not meet the diagnostic criteria for major depressive disorder. It is a strong risk factor for depression and is related to an increase in suicide and mortality. Studies suggest that acupuncture may be effective in the treatment of subthreshold depression, but no evidence has proven that the efficacy of acupuncture for subthreshold depression is a specific therapeutic effect or a placebo effect.

**Methods:**

This will be a prospective, randomized, controlled, and double-blind study of 64 patients with subthreshold depression. They will be randomly assigned as verum or minimal acupuncture group members. Patients in the verum acupuncture group will receive acupuncture at the acupoints, and those in the minimal acupuncture group will receive minimal acupuncture at non-acupoints. The interventions will be delivered over an 8-week period. The primary outcome measure will be the Hamilton Depression Scale-17 (HAMD-17). The secondary outcome measures will be the 9-item Patient Health Questionnaire (PHQ-9), 7-item Generalized Anxiety Disorder (GAD-7), and SF-12v2 Health Survey. The assessments will occur at baseline, 4 weeks, 8 weeks, and during a follow-up period.

**Discussion:**

The protocol uses a randomized controlled trial to examine the effectiveness of acupuncture for subthreshold depression and to further study the mechanisms of its effect.

## Background

Subthreshold depression refers to a state of mental sub-health that has depressive symptoms but does not meet the diagnostic criteria for major depressive disorder (MDD) in the Diagnostic and Statistical Manual of Mental Disorders (DSM) (1). According to the results of the American epidemiological survey (2), 20% of the general population has depressive symptoms that belong to subthreshold depression. Braam (3) surveyed 14,200 elderly people in 7 European cities and found that the prevalence of subthreshold depression is at least 2–3 times higher than that of depression, of which ~8% develop depression each year. In China, the incidence of subthreshold depression among college students has reached 36.56% (4). A survey by the World Health Organization showed that depression is the second leading cause of disability (5), and it will become the prime global disease burden in 2030 (6). Subthreshold depression is a strong risk factor for depression (7), which may occur alternately with MDD over time (8). Although the symptoms are mild, they are still related to an increase in suicide and mortality (9). In addition, the degree of depression is positively correlated with cardiovascular and cerebrovascular diseases, such as coronary heart disease and stroke (10). Therefore, timely detection, diagnosis, and treatment of subthreshold depression will delay or reverse the development of MDD to effectively reduce the harm of depressive symptoms. A systematic review showed that antidepressants had no significant advantage over placebo in patients with minor depression (11), and similar conclusions were drawn in randomized trials (12). Therefore, limited evidence suggests that antidepressants may be beneficial to patients with more severe depression (13) but are often accompanied by severe adverse reactions.

Acupuncture, as a non-drug therapy, has been widely used in the treatment of depression (14–16). A small sample study showed that electroacupuncture (EA) and cognitive behavioral therapy (CBT) could ameliorate the Hamilton Depression Scale-17 (HAMD-17), Center for Epidemiologic Depression scale (CES-D), and WHO Quality of Life-Brief version scores of subthreshold depression, but no significant differences were found between the EA and CBT groups (17). Another study showed that acupuncture can reduce HAMD-17 and CES-D scores compared with the blank control (18). These studies suggest that acupuncture may be effective in the treatment of subthreshold depression. Evidence has shown that placebo drugs or CBT can reduce depression symptoms, although it remains unclear whether the effect of acupuncture on subthreshold depression is a specific therapeutic effect or a placebo effect. Since no evidence has emerged to address this question, we designed this study.

## Methods

This protocol was designed according to the standard protocol items: recommendations for interventional trials (SPIRIT) checklist and Standards for Reporting Interventions in Clinical Trials of Acupuncture (STRICTA) 2010 checklist of information to include when reporting interventions in a clinical trial of acupuncture. The study protocol (version: 20210722-2.0) was approved by the Institutional Review Board (IRB) of the Affiliated Hospital of Shandong University of Traditional Chinese Medicine (2021-055-KY), and this study was registered in the Chinese Clinical Trial Registry (ChiCTR2100049660). If there are any changes in the study design, the Ethics Committee will be immediately informed.

### Trial Objective

Current studies have shown that acupuncture can relieve the clinical symptoms of subthreshold depression, but it is not clear whether the effect of acupuncture on subthreshold depression is caused by the placebo effect. Therefore, the objective of this study is to evaluate the efficacy of acupuncture in the treatment of subthreshold depression by comparing verum acupuncture and minimal acupuncture and to verify whether there is a placebo effect. In addition, we will explore the mechanism of acupuncture in the treatment of subthreshold depression.

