### Trial Design

This study will be a single center, randomized, double-blind clinical trial with two treatment groups (verum acupuncture and minimal acupuncture). The flow chart in Figure 1 shows more details regarding the clinical procedures.

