#### Minimal Acupuncture

Non-acupoints (Table 1) without antidepressant therapy will be used to provide acupuncture for subjects in the minimal acupuncture group. Acupuncturists will use sterile needles 0.30 × 25 mm in size punctured 2 mm in depth without achieving a Deqi sensation (feel nothing after the needle is punctured). The course of treatment will be the same as that of the verum acupuncture group. After the follow-up period, 24 sessions of acupuncture treatments will be compensated for free according to the subject's wishes.

**Table 1 T1:** Location of non-acupoints in minimal acupuncture group.

**Non-acupoints**	**Location**
NA1	In the outside of the forearm, 1 cm outside the midpoint of the line between Yangchi (TE4) and Waiguan (SI4)
NA2	In the outside of the forearm, 1 cm outside the midpoint of the line between Shousanli (LI10) and Quchi (LI11).
NA3	In the abdomen, 1 cm outside the midpoint of the line between Daheng (SP15) and Fushe (SP13)
NA4	In the outside of the calf, 1 cm below the midpoint of the line between Zusanli (ST36) and Yanglingquan (GB34)
NA5	In the back of the foot, the midpoint of the line between Qiuxu (GB40) and Jiexi (ST41)

*NA, non-acupoints*.

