#### Primary Outcome Measurement

The primary outcome will measure changes in the HAMD-17 scores between baseline and 8 weeks after randomization. The Hamilton Depression scale (22), developed by [name] in 1960, is a widely used depression scale. It includes cognitive impairment, block, despair, anxiety/somatization, sleep disorder, weight, and diurnal changes. It is mainly used to evaluate the severity of depressive symptoms in adult patients with depression and the curative effect before and after clinical trials. The higher the score, the more serious the degree of depression.

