### Statistical Analyses

R 4.0.5 software will be used for statistical analysis by an independent statistician who will not participate in the study. Two-tailed *p*-values < 0.05 will be considered statistically significant. Normally distributed continuous variables will be presented using the means and standard deviation, and non-normal variables will be presented as the medians and interquartile range. All efficacy analyses will be performed using the intent-to-treat (ITT). Missing data will be replaced according to the principle of the last observation carried forward method (28). The per-protocol (PP) population will be analyzed to determine the consistency of the results. The data before and after treatment in each group will be compared based on a paired *t* test or Wilcoxon signed-rank test, and the comparison between groups will be performed using an independent sample *t* test or Mann–Whitney *U* test. Categorical variables will be analyzed using the χ^2^ test or Fisher's exact test. For comparisons of the primary outcomes across the groups, we will use analysis of covariance with the baseline HAMD-17 to adjust. A generalized linear mixed model will be used for repeated measures, setting group and time as fixed factors and patient as a random factor; the interaction effects of group^*^time will be included in the model.

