The goal of this RCT is to assess the effectiveness of acupuncture compared with minimal acupuncture to prove whether there is a placebo effect for subthreshold depression. In addition, the gut-brain axis plays an important role in depression (36, 37). However, there is no evidence that acupuncture interferes with subthreshold depression through the gut-brain axis; therefore, we will collect blood and stool samples from the subjects to establish a biological sample bank. If our clinical trials prove that acupuncture in the treatment of subthreshold depression is not just a placebo, we will use this biological sample bank to explore the mechanism of acupuncture for subthreshold depression.

The primary limitation of our trial is that acupuncturists cannot be blinded. Second, as a preliminary exploratory study, this study was designed as a single center study. If the study is effective, we will conduct further multicenter research.

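### The stated aim of verifying a placebo effect is beyond a trial with two needled arms, which can estimate only the effect of verum beyond minimal acupuncture

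*Protocol article*

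**What the plan says.** The Trial Objective section gives two aims in one sentence: to evaluate the efficacy of acupuncture "by comparing verum acupuncture and minimal acupuncture and to verify whether there is a placebo effect". The Discussion states the goal again as "to assess the effectiveness of acupuncture compared with minimal acupuncture to prove whether there is a placebo effect for subthreshold depression".

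Trial Design lists two groups, verum and minimal acupuncture. The minimal group is also needled, on the same course, with "sterile needles 0.30 × 25 mm in size punctured 2 mm in depth without achieving a Deqi sensation". No untreated, waiting-list or usual-care group is described.

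The primary endpoint is fixed: "The primary outcome will measure changes in the HAMD-17 scores between baseline and 8 weeks after randomization". Statistical Analyses gives it a between-group method: "For comparisons of the primary outcomes across the groups, we will use analysis of covariance with the baseline HAMD-17 to adjust". The same section also plans within-group tests: "The data before and after treatment in each group will be compared based on a paired" t test or Wilcoxon signed-rank test. Participants enter with a HAMD-17 score from 7 to below 17, so the outcome scale is also the selection scale.

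**The concern.** To verify that a placebo effect exists, the response to minimal acupuncture has to be compared with the response to no needling. This trial does not make that comparison. Any placebo response shared by the two arms cancels in the verum-minus-minimal difference, so neither its existence nor its size can be recovered.

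The objective therefore leaves room for two unsupported conclusions. A null between-arm result could be taken to show that acupuncture works only as a placebo. A significant before-after change in the minimal arm could be taken to show that a placebo effect is present. The second matters because the paired test in the minimal arm is the only planned analysis that might appear to address the placebo aim directly.

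**Working it through.** **1. The plan's own figure.** Inputs from Sample Size Estimation: difference 4.87, SDs 1.99 and 7.18, 27 per arm, two-sided alpha 0.05, unequal-variance t test.

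- SE = sqrt((1.99² + 7.18²)/27) = sqrt(55.51/27) = 1.434
- Noncentrality = 4.87/1.434 = 3.40; Satterthwaite df = 29.97
- Power = 90.75%, as stated
- With 15% dropout: 27/0.85 = 31.8, so 32 per arm and 64 in total, as stated

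The arithmetic is right, but it concerns only the between-arm difference.

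**2. What the two arms identify.** Write the mean change in each arm as a sum:

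- minimal arm = placebo response + natural course + regression to the mean + any effect of shallow needling
- verum arm = placebo response + natural course + regression to the mean + effect of verum needling

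If blinding holds, so that placebo response is similar in both arms, the difference is the effect of verum needling minus any effect of shallow needling. The placebo term drops out. Within the minimal arm alone, one observed mean cannot separate four components.

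**3. How a paired test behaves with no placebo effect.** The documents give neither a natural change nor an SD of change, so both are assumed. Take 32 in the minimal arm and zero placebo effect. The noncentrality is m/(SD/sqrt(32)) for a natural improvement of m points, with 31 df and two-sided alpha 0.05. The probability of a significant paired t test is:

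| SD of change | m = 1 | m = 2 | m = 3 | m = 4 |
|---|---|---|---|---|
| 3 | 45% | 96% | >99% | >99% |
| 4 | 28% | 78% | 98% | >99% |
| 5 | 20% | 59% | 91% | 99% |
| 7.18 | 12% | 33% | 63% | 86% |

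The last row uses the protocol's placebo-group SD as if it were an SD of change. In a simulation with a shared 3-point improvement, SD 4, and neither a placebo nor a specific effect, each within-arm test was significant in about 98% of trials, while the between-arm test stayed at 5%.

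**4. Regression to the mean.** The entry window is cut at both ends. With assumed screening means of 8 to 16, SDs of 4 to 5 and reliability of 0.6 to 0.8, the expected change from this source runs from about -1.2 to +1.0 points (positive = improvement). It can go either way, so natural course may be the larger part.

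**5. What a null between-arm result would exclude.** 95% CI half-width with 32 per arm, without baseline adjustment:

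- SD 4 in both arms: 2.00 × 4 × sqrt(2/32) = 2.0 points
- SD 5 in both arms: 2.00 × 5 × sqrt(2/32) = 2.5 points
- SDs 1.99 and 7.18: 2.03 × sqrt(55.51/32) = 2.03 × 1.317 = 2.7 points

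A non-significant estimate is smaller than its half-width, so the upper limit is below twice the half-width: about 4.0, 5.0 and 5.3 points. At SD 4, any non-significant result excludes the planned 4.87. At the protocol's own SDs, an estimate between about 2.2 (4.87 - 2.67) and 2.67 is non-significant and does not exclude it. In all three cases smaller effects can remain.

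**The case against.** The strongest reply is that the phrase is loose but the question behind it is sound. The Background asks whether the effect of acupuncture is specific or a placebo effect, the Trial Objective opens in the same terms, and the Discussion makes the mechanism work conditional on showing that acupuncture is more than a placebo. Verum against minimal acupuncture, analysed by baseline-adjusted ANCOVA, can answer that in the positive direction. This stands, and it confines the defect to the literal placebo aim and to what a null result is taken to mean.

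A reader might go further and infer that the plan means to report a significant before-after change in the minimal arm as proof of a placebo effect, or p > 0.05 between arms as proof of no specific effect. The document says neither. It lists the paired tests as general before-after comparisons, and where it names the placebo question it ties it to the between-arm comparison. Misreading is a risk, not a stated intention.

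It is also fair that a single figure for the paired test would mislead. The result depends almost wholly on assumed values, and regression to the mean cannot be presumed to produce improvement under a two-sided entry window. Nor is a null result always too imprecise to be informative, since at SD 4 it would exclude the planned effect. The article also calls the trial a pilot, and it measures expectancy and blinding, which helps in interpreting non-specific effects. None of this supplies the missing comparison with no needling.

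**Conclusion.** The point holds in a limited form. As worded in the Trial Objective and Discussion, the aim to verify or prove a placebo effect is one this design cannot meet. The trial can estimate the effect of verum beyond minimal acupuncture. A positive difference, if blinding holds, supports more than a placebo. A null difference could reflect placebo response, natural course, active shallow needling or imprecision.

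The paired tests give no help. With no placebo effect at all, they are significant in about 12% to over 99% of trials across assumed natural improvements of 1 to 4 points and SDs of change of 3 to 7.18. That range illustrates the problem and is not a prediction. The half-width of 2.0 to 2.7 points likewise rests on assumed SDs or on the protocol's planning SDs, without the gain from baseline adjustment.

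The sample size calculation and the primary ANCOVA are not affected, and no third arm is needed once the objective is restated.

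**What to change.** - **Trial Objective and Discussion:** state the objective as the baseline-adjusted verum-minus-minimal difference in HAMD-17 change at week 8, with its 95% CI. Delete the aim of verifying or proving a placebo effect.
- **Statistical Analyses:** report within-group changes descriptively, as means with CIs, and base no efficacy or placebo conclusion on them.
- **Interpretation:** state that a non-significant difference does not establish a placebo-only effect, and that it is to be read from the CI against the planned 4.87 points.

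The cost is wording only: no new arm, participants or data. If recruitment has already finished, the changes can still be applied to the analysis and report, with the restatement of the objective disclosed. The downside is a more modest claim.

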### Trial Design

This study will be a single center, randomized, double-blind clinical trial with two treatment groups (verum acupuncture and minimal acupuncture). The flow chart in Figure 1 shows more details regarding the clinical procedures.

**Figure 1 F1:**
[figure not shown]
Flow chart of study design. M.I.N.I, Mini International Neuropsychiatric Interview; HAMD-17, Hamilton Depression Scale-17; PHQ9, The 9-item Patient Health Questionnaire; GAD-7, 7-item Generalized Anxiety Disorder; SF12v2, SF-12v2 Health Survey.

### Setting

The trial will be conducted at the preventive and health care center of the Affiliated Hospital of Shandong University of Traditional Chinese Medicine (Jinan, China).

### Participants

Participants will be recruited by advertisement. Interested volunteers can contact the research assistants by WeChat or phone. All volunteers will be screened by applicants according to the inclusion and exclusion criteria. The research assistants will introduce the research process, consent forms to the volunteers in detail, and the designated plan of each group. Eligible volunteers were invited to participate in the study, signed an informed consent form, and then arranged for a baseline assessment.

### Inclusion Criteria

Participants will be included if they meet the following criteria:

The Mini International Neuropsychiatric Interview (MINI version 5.0) will be used to identify subthreshold depression patients who have depressive symptoms but do not meet the major depression disorder criteria according to the Diagnostic and Statistical Manual of Mental Disorders (Fifth Edition) (DSM-V);Aged between 18 and 60 years;The score of HAMD-17:7 ≤ HAMD <17;No treatment related to depression has been received in the past 2 weeks;Antibiotics, probiotics, yogurt, and other fermented dairy products were not taken before random sampling;Voluntarily participating in this trial with a written informed consent form.

### Exclusion Criteria

Participants with the following conditions will be excluded:

Meeting the criteria for major depressive disorder, bipolar disorder, or psychotic disorder according to DSM-V;Patients with severe liver and kidney damage, severe arrhythmia, or cardiac insufficiency;Pregnant women;Depression caused by psychoactive, non-addictive substances, or brain diseases;Patients have suicidal attempt or behavior;Patients who cannot tolerate acupuncture;Patients who are difficult to communicate with or do not cooperate with the researcher;Other situations determined by the researchers to be unsuitable for observation.

### Elimination and Withdrawal Criteria

Misdiagnosis;Self-use of other related drugs, antibiotics, probiotics, yogurt, and other fermented dairy products;Subjects dropped out of the study, had difficulty cooperating with the treatment, or were lost to follow-up in the later stage.

### Observation Criteria That Would Stop the Trial

Cases with serious complications or other serious diseases during the study and if urgent measures are needed.The progression of disease during treatment.

### Sample Size Estimation

This pilot study aims to assess the efficacy of acupuncture for subthreshold depression as well as the feasibility of a further large clinical trial. The HAMD-17 was used as the main effect indicator to calculate the required sample size. According to relevant published literature (19, 20), the difference in HAMD-17 scores between the acupuncture and placebo groups was 4.87, and the standard deviation was 1.99 in the acupuncture group and 7.18 in the placebo group. Group sample sizes of 27 and 27 achieve 90.75% power to reject the null hypothesis of equal means and with a significance level (alpha) of 0.050 using a two-sided two-sample unequal-variance *t* test by PASS 15 software. Assuming a dropout rate of 15%, 64 participants are necessary, with 32 participants in each group.

### Randomization and Allocation Concealment

Independent statisticians will use the block randomization method with R 4.0.5 software and the blockrand R package. An independent clinical trial researcher will implement the allocation schedule using opaque sealed envelopes. A random number will be assigned after the participants meet all inclusion criteria and complete the baseline assessment. The Clinical Research Coordinator (CRC) will be responsible for enrolling participants, obtaining informed consent, and requesting randomization.

### Blinding

Blinding of acupuncturists is not possible due to the therapeutic characteristics of acupuncture; thus, the acupuncturist who provides treatment for patients is unable to be blind to treatment allocation. Participants and all other researchers will be blind to the treatment allocation plans, including data analysts and outcome assessors. To ensure the implementation of the blind method, patients will avoid communicating with each other during the trial period, and an isolatable treatment bed will be used for acupuncture treatment to avoid patients seeing treatment of others. Treatment groups will be defined as Group A and Group B during the statistical analysis of the data.

### Intervention

Verum acupuncture and minimal acupuncture will be performed by certified acupuncturists who have worked at least 5 years in clinics. Before the trial, all acupuncturists will be required to receive special training to fully understand the performance of the treatment and will receive a pamphlet detailing the standardized operation. The training contents include acupoint and non-acupoint positioning methods, acupuncture manipulation and minimal acupuncture manipulation. A study investigator will communicate with the participants every week in advance of trial commencement via phone and WeChat to remind them of their visit. Other antidepressant treatments will be prohibited during the trial.

